## 2. Methods

### 2.1. Study Design and Setting

This is a prospectively planned, open-labeled, parallel-grouped, single-centered clinical trial. The trial will be conducted at the outpatient care of the Cardiology Department at the Dongzhimen Hospital, Beijing University of Chinese Medicine in China. The staff of the department will be informed of the trial and they will help researchers to recruit participants. The trial is conducted by the ethical principles laid down in the Declaration of Helsinki, the Guideline for Good Clinical Practice, and local laws. The informed consent form will be obtained from all participants before any trial-related procedures were conducted, enrolled after a complete and extensive description of the study. The trial was approved by the Ethics Committee of Dongzhimen Hospital, Beijing University of Chinese Medicine (Supplementary File 1). We present the protocol in accordance with the SPIRIT reporting checklist (Standard Protocol Items Recommendations for Interventional Trials) (Supplementary File 2).

In terms of research methods, we refer to and improve one of our previous experimental designs [14]. 480 participants will be randomly assigned to either an aspirin group, a Xuesaitong group, or drug combination group at a ratio of 1: 1: 1. Participants in the aspirin group will be administered aspirin (100 mg, qd) orally 30 min after breakfast, participants in the Xuesaitong group will be administered Xuesaitong soft capsule (contains PNS and excipients; 200 mg, tid) orally 30 min after breakfast, and participants in the drug combination group will be administered both drugs above. The two drugs should be taken half an hour apart, and aspirin should be taken first. All treatment courses will last for 30 days. Blood samples will be acquired 30 min before administration on day 1 and 30 min after administration on day 30. The volume of each blood sample is 4 mL. And fecal samples will be collected on days 1 and 30. Details of patient follow-up are summarized in Table 1 and Figure 1.

### 2.2. Participants

The detailed inclusion, exclusion, and termination criteria are shown in Table 2.

### 2.3. Randomization

This is a single-center clinical trial with a sample size of 480. They were randomly divided into three groups equally. The randomization code will be developed by the statistics office of Dongzhimen Hospital. The trial cases were separated into three arms. The research pharmacy will randomize the participants based on the master randomization list. A third party will join to ensure the allocation concealment.

### 2.4. Sample Size

The sample size was calculated based on the primary outcome (platelet aggregation rate). For power analysis, the primary outcome was assumed to be 38.72% in the aspirin group [15], and 37.79% in the Xuesaitong group [16]. Given a type I error at 0.05 and type II error at 0.2, the required sample size was 131 per arm. Expecting 20% dropout rate, we planned to enroll 160 subjects.

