### 2.8. Planned Outcomes and Measurements

The primary outcomes, secondary outcomes, and safety outcomes are summarized in Table 4.

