### 2.10. Data Management and Statistical Analysis Plan

We use EDC system to collect the data. The system administrator establishes the eCRF and conducts logic verification and range checks for data values. Two investigators fulfill double-data entry.

The analysis will be performed in a modified intention-treat population, which included all randomized participants who received at least one dose of Xuesaitong or aspirin. Continuous variables are presented as the mean ± SD and categorical variables as number and percentage. Comparisons between treatment groups were assessed using Student's *t*-test or Wilcoxon rank-sum test for continuous variables. Comparisons were assessed using the Fisher exact test for categorical variables. Data for patients who were lost to follow-up were censored at the time of the last contact. A multivariable Cox proportional-hazards regression analysis that included center and treatment as independent variables was conducted, and the results are expressed as hazard ratio (HR) with 95% confidence interval (CI). The incidence of adverse events was compared using the chi-squared test. *P* < 0.05 (two-sided) was considered to be statistically significant. All analyses were conducted using SPSS software 26.0.

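### The 80% power in section 2.4 is derived from the two single-drug arms, so it does not apply to combination versus single use, and the printed inputs do not determine 131 per arm

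*Protocol article*

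**What the plan says.** Section 2.4 names one endpoint for sizing: "The sample size was calculated based on the primary outcome (platelet aggregation rate". Its assumed values cover two of the three arms: "the primary outcome was assumed to be 38.72% in the aspirin group [15], and 37.79% in the Xuesaitong group [16". It then concludes: "Given a type I error at 0.05 and type II error at 0.2, the required sample size was 131 per arm". After an allowance of 20% for dropout it plans 160, which agrees with the total in section 2.1, where 480 people are split equally over three arms (480/3 = 160).

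The section gives no value for the combination arm, no SD and no margin. It does not say whether the 0.05 is one-sided or two-sided, or whether the hypothesis is superiority or noninferiority.

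Other parts of the article bear on this:

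- The Introduction calls the trial a noninferiority trial and, in the same sentence, gives its aim as finding out whether the combination is superior to single use in efficacy and safety.
- The Abstract and Table 4 list two primary outcomes, platelet aggregation rate and calprotectin.
- Section 2.10 plans two-group tests ("Comparisons between treatment groups were assessed using Student's" t-test, or the Wilcoxon rank-sum test) with the criterion P "< 0.05 (two-sided) was considered to be statistically significant".

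**The concern.** A power statement belongs to a particular contrast, hypothesis and variance. Here the only contrast with numbers is aspirin against Xuesaitong, while the Introduction, the Abstract and the Discussion all frame the conclusions around the combination. A reader who sees 80% power will take it to cover combination versus aspirin. Nothing in section 2.4 supports that.

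The second difficulty is that 131 cannot be traced. The assumed difference is under one percentage point, and the section does not say what kind of test it was meant for. If the combination result turns out null, or is called noninferior, the reader cannot tell from this section what difference the trial was built to detect or exclude.

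**Working it through.** **Inputs.** From section 2.4: 38.72% (aspirin), 37.79% (Xuesaitong), type I error 0.05, type II error 0.2, 131 per arm, 20% dropout, 160. From section 2.10: two-sided 0.05 and a two-group t-test. The SD and the margin are not given, so they are solved for or varied as assumptions. Normal quantiles: 1.960 (two-sided 0.05 or one-sided 0.025), 1.645 (one-sided 0.05), 0.8416 (80% power).

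**1. The difference used.** 38.72 − 37.79 = 0.93 points. It lies between the two single-drug arms. No difference involving the combination can be formed from the printed values, so power for that contrast cannot be computed from this section.

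**2. Attempt to reproduce 131 as superiority of means.** From n = 2·SD²·(z_α + z_β)²/Δ², it follows that SD = Δ·√(n/2)/(z_α + z_β).

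- Two-sided 0.05: 0.93 × √65.5 / (1.960 + 0.8416) = 7.527/2.8016 = 2.69 points (2.68 by the noncentral t).
- One-sided 0.05: 7.527/(1.645 + 0.8416) = 3.03 points (3.02 by the noncentral t).

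Sensitivity at 131 per arm and two-sided 0.05, with power = Φ(0.93/(SD·√(2/131)) − 1.960) and all SDs assumed:

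| SD (points) | Power | n per arm for 80% |
|---|---|---|
| 3 | 70.8% | 164 |
| 5 | 32.5% | 454 |
| 10 | 11.4% | 1,815 |
| 15 | 7.2% | 4,084 |

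**3. Attempt to reproduce 131 as noninferiority of means.** The requirement is (margin + favourable true difference)/SD = (z_α + z_β)·√(2/n).

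- One-sided 0.025: 2.8016 × √(2/131) = 0.346.
- One-sided 0.05: 2.4865 × √(2/131) = 0.307.

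Any margin and SD in that ratio return 131. For example, at an assumed SD of 10 and one-sided 0.025, the margin is 3.46 points if the true difference is zero, or 3.46 − 0.93 = 2.53 points if the 0.93 is a favourable true difference.

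So 131 is compatible with SDs from under 3 points to 10 or more, depending on which unstated hypothesis is chosen.

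**4. Dropout.** 131/(1 − 0.20) = 163.75, that is 164. Multiplying instead gives 131 × 1.2 = 157.2, that is 158. Neither is 160. In the other direction, 160 × 0.80 = 128 evaluable per arm, three short of 131.

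**5. What the planned size gives.** With 128 evaluable per arm, zero true difference, one-sided 0.025 and 80% power, the margin that can be excluded is 2.8016 × SD × √(2/128) = 0.350 × SD:

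- assumed SD 5: 1.75 points
- assumed SD 10: 3.50 points
- assumed SD 15: 5.25 points

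As the arms are equal in size, the same figures apply to any pairwise contrast with that SD.

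**The case against.** The strongest reply is that a journal article condenses. The SD, the margin and a calculation for calprotectin may all be in the full protocol, and the assumed values come from two cited studies that are not at hand. This stands as far as it goes. The absence of an SD or margin is not the finding, nor is the lack of a separate calprotectin calculation. It does not reach the main point, because section 2.4 names the two arms it used, and an unseen SD or margin would not turn aspirin versus Xuesaitong into a combination contrast.

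Three stronger readings are tempting, and the documents do not support them.

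- A reader might infer that 80% power holds only if the SD is about 2.7. That is true only for a two-sided superiority test of means. The trial is labelled noninferiority, and step 3 of the working shows that an unstated margin allows a much larger SD. The power table is a sensitivity analysis and does not demonstrate a shortfall.
- A reader might infer that the percentages were treated as binary with a noninferiority margin near 14 points, since such a formula lands close to 131. The article states no such margin. With margin, alpha and outcome type all free, some combination will always return 131. This is conjecture and no basis for criticism.
- A reader might infer that a null result would be uninterpretable, or that the stated power fits no planned test. Section 2.10 does not exclude aspirin versus Xuesaitong, and a confidence interval can be read whatever the planning assumptions were.

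It can also be objected that keeping 160 per arm prejudges the answer before an SD is known. The fix therefore asks only for an honest statement of what that size delivers.

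**Conclusion.** The point holds in two parts of unequal strength, plus a minor discrepancy.

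The firmer part needs no outside figure: the stated 80% power rests on the two monotherapy arms, 0.93 points apart, and does not apply to combination versus single use, which is the stated aim.

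The second part is that the printed inputs do not determine 131. It corresponds to an SD of 2.69 or 3.03 points under superiority of means (two-sided or one-sided 0.05), or to a margin plus favourable difference of 0.346 or 0.307 SD under noninferiority (one-sided 0.025 or 0.05). The powered hypothesis therefore cannot be identified from this article. No arithmetic error in 131 has been shown, and none is claimed.

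The dropout step is slightly inconsistent: 160 less 20% is 128, not 131.

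These results assume a 1:1 comparison of two means under the normal approximation. The SDs of 3, 5, 10 and 15 points are assumptions, as the article gives none.

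**What to change.** Keep 160 per arm. Remove the 80% power claim that rests on aspirin versus Xuesaitong, and rewrite section 2.4 for combination versus aspirin, with platelet aggregation as a continuous variable. The paragraph should state:

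- whether the hypothesis is superiority or noninferiority, with the difference or margin;
- the SD and its source;
- one alpha convention consistent with the two-sided 0.05 of section 2.10 (one-sided 0.025 if noninferiority);
- the power or detectable margin at about 128 evaluable per arm, in the form shown in step 5 of the working;
- the same precision statement for calprotectin, the other primary outcome.

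The cost is one rewritten paragraph, with no added enrolment. The downside is that the stated power or margin may look less favourable than the present 80%.

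### Minor: at the stated 20% dropout, 160 enrolled per arm leaves 128, which is 3 per arm short of the 131 the plan requires

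*Protocol article*

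**What the plan says.** Section 2.4 (Sample Size) gives the error rates, "Given a type I error at 0.05 and type II error at 0.2", and concludes that "the required sample size was 131 per arm". The next sentence allows for losses: "Expecting 20% dropout rate, we planned to enroll 160 subjects".

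That sentence does not say whether 160 is per arm or in total. Other sections settle it. Section 2.3 (Randomization) says "This is a single-center clinical trial with a sample size of 480" and "They were randomly divided into three groups equally"; section 2.1 also gives 480 at a 1:1:1 ratio. Since 480/3 = 160, the figure is per arm.

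The section shows no formula for the step from 131 to 160.

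**The concern.** An allowance for dropout is meant to ensure that the required number remains after the expected losses. Three figures stand side by side in section 2.4 (131 required, 20% lost, 160 enrolled), and the third does not follow from the first two.

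The losses matter for the outcome that sized the trial. Table 1 schedules platelet aggregation on day 1 and day 30 only, so a participant who leaves before day 30 has no post-treatment value. If the plan's own forecast comes true, the number with observed data falls below the number the plan says it needs, and the stated power is not quite reached even if every other assumption is right.

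**Working it through.** **Inputs**

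- Required per arm: 131 (section 2.4), read as the number remaining after dropout, since the allowance is applied to it.
- Dropout: 20% (section 2.4).
- Enrolled per arm: 160 (section 2.4; 480/3 from sections 2.1 and 2.3).
- Type I error 0.05 and type II error 0.2, so power 80% (section 2.4; sidedness is not given there).

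**Step 1. Can 160 be reproduced?**

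- Dividing by the retained fraction: 131/(1 - 0.20) = 163.75, so 164.
- Adding 20% to the requirement: 131 x 1.20 = 157.2, so 158.

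Neither gives exactly 160. It lies 4 below one result and 2 above the other, and either could have been rounded to a convenient number. The figures cannot tell the two routes apart.

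**Step 2. What 160 leaves**

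- 160 x (1 - 0.20) = 128 per arm.
- Shortfall: 131 - 128 = 3 per arm, or 3/131 = 2.3%; over three arms, 9.

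**Step 3. What full cover needs**

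- 164 x 0.80 = 131.2, which is enough; 163 x 0.80 = 130.4, which is not.
- Total: 164 x 3 = 492, which is 12 more than 480.

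**Step 4. The dropout that 160 does cover**

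- 1 - 131/160 = 18.1%.

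**Step 5. Effect on power (conditional)**

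Assume that 131 per arm gives exactly 80% power in a two-arm comparison, using the normal approximation. The sum of the two normal quantiles then scales with the square root of n, and sqrt(128/131) = 0.9885.

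- Two-sided 0.05: (1.960 + 0.842) x 0.9885 - 1.960 = 0.809, so power is 79.1%.
- One-sided 0.05: (1.645 + 0.842) x 0.9885 - 1.645 = 0.813, so power is 79.2%.

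The loss is 0.8 to 0.9 of a percentage point.

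**The case against.** The strongest reply is that the gap is too small to matter. It is 3 participants in 131, and 160 is within 4/164 = 2.4% of the fully covered number. No dropout forecast is accurate to the two points that separate 18% from 20%. This stands, and it is why the point is minor. It does not make the sentence correct, because rounding an enrolment target down gives away part of the cover it was meant to provide.

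A second reply is that the 79% is not independent evidence. This also stands. Section 2.4 states no SD, noninferiority margin or sidedness, so the figure is back-solved from 131 and says only how 128 compares with 131. A reader might take it as the trial's actual power, but the document does not support that. That 131 cannot itself be reproduced from section 2.4 is a separate matter; the inconsistency here holds whatever 131 rests on.

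A third reply is that the modified intention-to-treat population in section 2.10 keeps everyone who took at least one dose. It keeps them in the population but does not supply a day 30 value.

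Two stronger readings are tempting and should not be adopted:

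- A reader might infer that the sponsor multiplied by 1.2 when it should have divided by 0.8. The article shows no formula, multiplication gives 158 and not 160, and 163.75 rounded down to 160 fits as well.
- A reader of section 2.4 alone might take 160 as the trial total. The sentence before it speaks of numbers per arm, and 480 in three equal groups settles the question. The missing words are a clerical slip.

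**Conclusion.** The point holds as a minor error of statement. Under the plan's own figures, 160 per arm leaves 128 and not 131; full cover at 20% dropout would take 164 per arm (492 in total); and 160 is enough only up to about 18% dropout. This part rests on nothing beyond the printed numbers and the ordinary meaning of a dropout rate as a share of those enrolled.

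The consequence for power is under one percentage point, from 80% to about 79%, on the assumption that 131 delivers 80%. The shortfall does not threaten the trial, and the document does not allow any conclusion about how it arose.

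**What to change.** Keep 480 and restate the last sentence of section 2.4 along these lines: *We plan to enrol 160 participants per arm (480 in total), leaving 128 evaluable per arm at 20% dropout (131 at about 18%).* Add the power for 128 per arm, computed by the sponsor from the inputs that produced 131; it cannot be computed from the article alone. The same edit supplies the missing words per arm.

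The cost is one sentence and a slightly less favourable stated power. No further enrolment is needed. Full cover at 20% dropout would instead take 12 more participants, which a gain of less than one point of power hardly justifies.

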### 2.5. Interventions

The dose and duration of medication in each group are illustrated in Table 3.Aspirin enteric-coated tablets (100 mg, qd) (Bayer S.p.A): a widely used antiplatelet medicationXuesaitong soft capsule (200 mg, tid) (Kunming Huarun Shenghuo Co. Ltd.): the main ingredient of the Xuesaitong soft capsule is Panax notoginseng saponins (PNS), which is commonly used in preventing and treating blood stasis, to prevent cardiovascular disease

### 2.6. Combination

Participants are not allowed to take any kind of herbal or chemical medication which have the pharmacological effects of activating blood circulation, preventing platelet aggregation, or anti-inflammatory activityParticipants with angina pectoris could take isosorbide mononitrate. In addition, participants could take other medications that have no known drug-drug interaction with aspirin or Xuesaitong soft capsule

### 2.7. Sample Collection

#### 2.7.1. Aspirin Group

Participants should take aspirin with 200 mL of warm water on an empty stomach for 30 consecutive days.

#### 2.7.2. Xuesaitong Group

Participants should take Xuesaitong soft capsule with 200 mL of warm water on an empty stomach for 30 consecutive days.

#### 2.7.3. Drug Combination Group

Participants should take aspirin and Xuesaitong soft capsule on an empty stomach for 30 consecutive days. The interval between taking medicine is 30 minutes.

In all three groups, blood sampling will be carried out before administration on day 1 and after administration on day 30, and fecal samples will be collected on days 1 and 30.

### 2.8. Planned Outcomes and Measurements

The primary outcomes, secondary outcomes, and safety outcomes are summarized in Table 4.

### 2.9. Study Quality Control

Throughout the trial, each participant will be subject to safety monitoring. All the adverse events occurring will be transferred to the office of the clinical trial institution and Ethics Committee, who will review the events and adjudicate them with regards to causality.

We set DSMB (Data and Safety Monitoring Board) for this trial. The member of DSMB comprises physicians, clinical pharmacists, trial methodology experts, statistical experts, and members of the ethics committee, who will conduct risk assessment and safety analysis according to program termination criteria. Also, they will supervise the trial according to a manual of the procedure that has specific information and details for clinical research and laboratory tasks. DSMB are fully blinded to the study intervention reviews and adjudicates adverse events.

### 2.10. Data Management and Statistical Analysis Plan

We use EDC system to collect the data. The system administrator establishes the eCRF and conducts logic verification and range checks for data values. Two investigators fulfill double-data entry.

The analysis will be performed in a modified intention-treat population, which included all randomized participants who received at least one dose of Xuesaitong or aspirin. Continuous variables are presented as the mean ± SD and categorical variables as number and percentage. Comparisons between treatment groups were assessed using Student's *t*-test or Wilcoxon rank-sum test for continuous variables. Comparisons were assessed using the Fisher exact test for categorical variables. Data for patients who were lost to follow-up were censored at the time of the last contact. A multivariable Cox proportional-hazards regression analysis that included center and treatment as independent variables was conducted, and the results are expressed as hazard ratio (HR) with 95% confidence interval (CI). The incidence of adverse events was compared using the chi-squared test. *P* < 0.05 (two-sided) was considered to be statistically significant. All analyses were conducted using SPSS software 26.0.

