**Methods:**

This trial is a prospectively planned, open-labeled, parallel-grouped, single-centered clinical trial. A total of eligible 480 participants will be randomly allocated into three groups: aspirin group, Xuesaitong group, and drug combination group at a ratio of 1 : 1 : 1. The primary outcome is the change of platelet aggregation rate and calprotectin activity. Secondary outcomes include PAC-1, P-selectin, P2Y12, I-FABP activity, and fecal occult blood. *Discussion*. The results of the study are expected to provide evidence of high methodological and reporting quality on the synergy function of Xuesaitong and aspirin upon the antiplatelet and anti-gastrointestinal injury effect for CHD. It also provides an experimental basis for clinical rational drug combination therapy. *Trial Registration*. This trial was registered in the Chinese Clinical Trail Registry, ChiCTR2000036311, on 22 August 2020, http://www.chictr.org.cn/edit.aspx?pid=58798&htm=4.

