## Figures and Tables

**Figure 1 fig1:**
[figure not shown]
A schematic flowchart of the clinical trial.

**Table 1 tab1:** Flowchart of a patient follow-up

Group	Screening D-7 to D1	D1	D30	D31 closeout
Patient information	X			
Physical examination	X	X		X
Vital signs	X			X
Blood routine; serum biochemistry; urine routine; stool routine; coagulation routine	X^1^	X^1^		X^1^
ECG	X			X
Stool biomarkers (calprotectin; I-FABP)		X	X	
Blood biomarkers (platelet aggregation; P2Y12; PAC-1; P-selectin)		X	X	

D: day; ECG: electrocardiogram; I-FABP: intestinal fatty acid-binding protein; PAC-1: platelet-associated complement 1. ^1^If the abnormality of this program is clinically significant, if it occurs before screening and at baseline, the subjects will be excluded directly. If it occurs during the observation period of administration, the retest will be followed up until the examination is normal or the abnormality is considered by the study doctor to be of no clinical significance.

**Table 2 tab2:** Inclusion, exclusion, and termination criteria.

Criteria
*Inclusion criteria*
(1) 45–75 years of age without gender restriction
(2) Meet the diagnostic criteria of CHD
(3) Meet the diagnostic criteria of grade I–II angina
(4) Meet the diagnostic criteria of blood stasis
(5) Meet the diagnostic criteria of stable angina pectoris
(6) Take regular aspirin (enteric-coated) for at least one year (the incidence of bleeding events, adverse events (AEs), and adverse reactions will be noted)
(7) Calprotectin in stool is above 50* μ*g/g
(8) Before the study start, patients and their families are fully informed and voluntarily willing to sign an informed consent

*Exclusion criteria*
(1) Mental or physical disorders
(2) Pregnant, menstruating, and breastfeeding women
(3) Severe heart disease and severe cardiopulmonary dysfunction
(4) Severe primary diseases, such as cancer, liver and renal damage, and multiple organ failure
(5) Poorly controlled hypertension (>160/100 mmHg)
(6) Current participation in another clinical trial or participation in another clinical trial within three months
(7) Having underwent surgery within eight weeks
(8) Having drug allergy history or allergic constitution
(9) Diabetes
(10) Status epilepticus
(11) Unstable vital signs
(12) Combined with serious infection, infectious diseases
(13) Acute intestinal infection
(14) Unsuitability or poor compliance for this trial

*Termination criteria*
Participant termination

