(1) Serious adverse events occur or having obvious abnormal value of the laboratory tests
(2) The investigators believe someone's trial needs to be terminated because of medical, safety, or GCP considerations
Trial termination
(1) Half of the participants have mild adverse events other than gastrointestinal reactions
(2) The investigators believe it is necessary to abort the trial for medical or safety purposes

**Table 3 tab3:** Dose and duration of medication.

Group	Medication	Dose and method	Duration
Aspirin group	Enteric-coated aspirin	100 mg, q.d., oral	30 days
Xuesaitong group	Xuesaitong soft capsule	200 mg, t.i.d., oral	30 days
Drug combination group	Xuesaitong soft capsule + enteric-coated aspirin	100 mg q.d. oral aspirin and 200 mg t.i.d. oral Xuesaitong soft capsule	30 days

**Table 4 tab4:** Clinical outcomes of the trial.

Items
*Primary outcomes*
Primary outcomes of improving efficacy
Platelet aggregation rate (platelet aggregation analyzer)
Primary outcomes of reducing gastrointestinal side effects
Change in calprotectin activity (ELISA) [17]

*Secondary outcomes*
Secondary outcomes of improving efficacy
(1) Change in PAC-1 activity (flow cytometry)
(2) Change in P-selectin activity (flow cytometry)
(3) Change in P2Y12 acceptor activity (flow cytometry)
Secondary outcomes of reducing gastrointestinal side effects
(1) Change in I-FABP activity (ELISA) [18]
(2) Change in fecal occult blood

*Safety outcomes*
(1) Serum biochemistry
(2) Blood routine
(3) Urine routine
(4) Stool routine
(5) ECG

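### The primary outcomes are compared without baseline adjustment although day-1 values are collected, and platelet aggregation is a change in the Abstract but carries no such label in Table 4 and is sized on levels

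*Protocol article*

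**What the plan says.** **Analysis.** Section 2.10 of the protocol article reads "Comparisons between treatment groups were assessed using" Student's t-test or "Wilcoxon rank-sum test for continuous variables". The only model with covariates is a time-to-event one: "A multivariable Cox proportional-hazards regression analysis that included center and treatment as independent variables was conducted". It has no baseline marker value in it and does not suit a continuous marker read on day 30.

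**Endpoint.** The Abstract says "The primary outcome is the change of platelet aggregation rate and calprotectin activity". Table 4 lists the first primary outcome as "Platelet aggregation rate (platelet aggregation analyzer" and the second as "Change in calprotectin activity (ELISA) [17". Calprotectin and all five secondary outcomes are labelled as changes in that table; platelet aggregation alone is not.

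**Sample size.** Section 2.4 works from two percentages: "the primary outcome was assumed to be 38.72% in the aspirin group [15], and 37.79% in the Xuesaitong group [16".

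**Measurements.** Table 1 schedules "Blood biomarkers (platelet aggregation; P2Y12; PAC-1; P-selectin" on D1 and D30, and the stool biomarkers likewise. Sections 2.1 and 2.7 confirm blood and fecal sampling on both days.

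**The concern.** Two things go together here.

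First, the outcome on which the trial is sized can be read as the day-30 level or as the change from day 1. These are different test statistics with different variances, and they can disagree on the same data. If the choice is still open when the data arrive, it can be made in favour of the better result. Because the trial is open-label, fixing the choice beforehand matters more.

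Second, whichever reading is meant, a two-sample test on it does not make the best use of the day-1 value. A day-30 comparison ignores it. A change score uses it with a fixed coefficient of 1, which is too large when the two visits are only moderately correlated. At stake are the width of the confidence interval on both primary outcomes and clarity about which result is the primary one.

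**Working it through.** **Inputs from the documents.** Levels 38.72% and 37.79%, type I error 0.05, type II error 0.2, 131 per arm (section 2.4); two-sided testing (section 2.10); equal allocation (Abstract).

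**Inputs not in the documents.** The standard deviation (SD) and the correlation r between day 1 and day 30. Values of r below are assumptions. Equal variance at both visits is also assumed.

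**1. The plan's own figure.** The 131 cannot be reproduced from what section 2.4 states, since no SD is given. Treated as a comparison of two mean levels, the difference is 38.72 − 37.79 = 0.93 points. The SD that would return 131 is 0.93 × √(131/2) / (1.960 + 0.842) ≈ 2.69 points (two-sided). This is an implied value. It is used below only as a reference: suppose that 131 per arm gives 80% power for an unadjusted comparison of levels.

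**2. Variance per patient, relative to the day-30 level.**
- Day-30 level: 1
- Change score: 2(1 − r)
- ANCOVA: 1 − r²

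Hence ANCOVA/change = (1 − r²) / [2(1 − r)] = (1 + r)/2, and ANCOVA/level = 1 − r².

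| r (assumed) | Change/level | ANCOVA/change | ANCOVA/level |
|---|---|---|---|
| 0 | 2.00 | 50% | 100% |
| 0.3 | 1.40 | 65% | 91% |
| 0.5 | 1.00 | 75% | 75% |
| 0.7 | 0.60 | 85% | 51% |

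**3. Power at 131 per arm under the reference in step 1.** Power = Φ(2.802/√v − 1.960), where v is the relative variance.

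| r (assumed) | Level | Change | ANCOVA |
|---|---|---|---|
| 0 | 80% | 51% | 80% |
| 0.3 | 80% | 66% | 84% |
| 0.5 | 80% | 80% | 90% |
| 0.7 | 80% | 95% | 98% |

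The level/change choice therefore moves power in either direction, depending on r.

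**4. Cost of leaving the choice open.** Under no true difference, the level and change statistics have correlation √((1 − r)/2), which is 0.59, 0.50 and 0.39 at r = 0.3, 0.5 and 0.7. The chance that at least one of the two two-sided 5% tests is significant is then 8.8%, 9.1% and 9.4%. This is for one pairwise comparison, and only if the better of the two results were reported.

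**5. Why ANCOVA makes the choice harmless.** Write the day-30 value as Y1 and the day-1 value as Y0. If Y1 = a + τ·(treatment) + b·Y0 + error, subtracting Y0 from both sides gives Y1 − Y0 = a + τ·(treatment) + (b − 1)·Y0 + error. The estimate of τ, its standard error and its p-value are the same in both. Only the coefficient of Y0 differs.

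**The case against.** Four points deserve a fair hearing.

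- **The stated tests are valid.** Under randomisation they are unbiased, and chance baseline imbalance is already covered by their error rate. This stands: the loss is one of efficiency. Covariate adjustment is often left to a statistical analysis plan that is not shown here. But section 2.10 names the unadjusted tests outright, so the point does not rest on silence.
- **The mismatch may be only a label.** Table 4 may be abbreviated, and levels taken from literature do not prove that a level analysis is meant. That is possible, and a reader who inferred that the sponsor intends to pick the definition after seeing results would go beyond the text. The text shows only that the definition is not settled.
- **The gain may be small.** No correlation is given, and equal variances are doubtful. Entry requires calprotectin above 50 μg/g, which truncates its baseline and may weaken its correlation with day 30. It also requires at least a year of regular aspirin, while one arm then receives Xuesaitong without aspirin. This stands as a limit on the figures. It does not reverse the direction: in large samples, for two arms of equal size, ANCOVA is no less precise than either unadjusted comparison, even if the visit variances differ.
- **Skew in calprotectin.** It is tempting to say that a few large values would drive the calprotectin result. The documents do not support that. They give no distribution, and section 2.10 allows a rank-sum test, which limits the pull of extreme values.

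**Conclusion.** The point holds as an improvement that should be made before analysis; it does not invalidate the trial. Two facts are established from the text: the continuous primary outcomes are compared with no baseline term although day-1 values are collected, and the platelet outcome is described inconsistently across the Abstract, section 2.4 and Table 4.

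The size of the efficiency loss is unknown. The ranges worked out above rest on assumed correlations and equal visit variances. A reader might take one cell, such as the 25% variance reduction at r = 0.5, as the expected gain; the documents do not support any single figure.

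Two further inferences should be resisted. Calprotectin is described as a change in both the Abstract and Table 4, so it has no inconsistency to repair and need not be redefined as a day-30 level. And ANCOVA does not by itself mend the wording: it makes the treatment effect the same under either reading, but the three places must still agree.

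**What to change.** 1. Choose one definition of the platelet aggregation outcome and use it in the Abstract, section 2.4 and Table 4, keeping the registered outcome consistent with it. Leave calprotectin as a change.
2. In section 2.10, make the primary analysis of both primary outcomes an ANCOVA with treatment and the day-1 value of the same marker. Report the baseline-adjusted between-arm difference with its 95% confidence interval. Use the same model for the continuous secondary markers.
3. Optionally, prespecify a log scale for calprotectin. The small downside is that the effect becomes a ratio rather than a raw change.

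The cost is a change of wording made before the data are analysed. The day-1 samples are already scheduled, so no patient, visit or assay is added. If the chosen platelet definition differs from the one in the Abstract, it changes the description of a primary outcome in a registered trial and should be documented as such; keeping the Abstract's definition avoids this.
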